#### Interventions

Appropriate preparation, positioning and surgical technique will be left to the discretion of the operating surgeon, as per their normal clinical practice. Participants will be randomly allocated to one of two treatment groups:

Group 1: Cemented hemiarthroplasty. Replacement of the femoral head and neck with a cemented femoral stem and head as per NICE guidance; the current standard-of-care (control) intervention.

Group 2: Modern uncemented hemiarthroplasty. Replacement of the femoral head and neck with a modern (hydroxyapatite coated) uncemented hemiarthroplasty; the alternative intervention.

Both types of hip replacement are used routinely throughout the NHS. While the principles of both cemented and uncemented arthroplasty are inherent in the technique, the surgical approach and other technical aspects of the surgery will be left to the discretion of the senior operating surgeon as per their normal practice. This will ensure that the results of this pragmatic trial can be extrapolated broadly across the NHS.

### Outcomes and data management

Personal data collected during the study will be handled and stored in accordance with the 1998 Data Protection Act, which requires data to be anonymised as soon as it is practical to do so. The data collected from participants will be entered in linked-anonymised form to the trial database. All electronic patient-identifiable information will be stored on a secure, password-protected database at the University of Oxford, accessible only to the research team. Any paper copies of identifiable data, and corresponding reidentifying links to the participant trial ID, will be stored separately, in a locked cabinet in an access-restricted part of the Kadoorie Centre, John Radcliffe Hospital, Oxford. The study databases will be developed by the trial programmer and all specifications agreed between the trial programmer, statistician and trial manager and other relevant members of the trial team. The procedure for data entry will be documented in the data management plan. As per routine clinical care, the existing National Hip Fracture Database (NHFD) dataset will be collected via telephone interview or postal questionnaire. We will send data collected at follow-up to the NHFD via a secure email account for them to upload using the participant’s date of birth and NHS number as identifiers.

#### Primary outcome measure

The study primary outcome measure is EuroQol 5 dimensions 5 levels (EQ-5D-5L) index score at 4 months postinjury. The index score is derived from the five health state domains using the crosswalk value data sets.^6^ EQ-5D-5L is a validated, self-rated instrument comprising a Visual Analogue Scale (VAS) measuring health and a health status instrument, consisting of a five-level response (no problems, some problems, moderate problems, severe problems and unable) for five domains related to daily activities^7^: (1) mobility, (2) self-care, (3) usual activities, (4) pain and discomfort and (5) anxiety and depression. The EQ-5D-5L instrument^7^ facilitates the generation of a utility score from a person’s HRQoL, which refers to the preference that individuals have for any particular set of health outcomes. As per the current NICE position statement, the responses to the EQ-5D-5L will be converted into multiattribute utility scores using an approved ‘cross-walk’ to the 3 L instrument and its established time trade-off utility algorithm for the UK population.^8^ A respondent’s EQ-VAS gives self-rated health on a scale where the endpoints are labelled ‘best imaginable health state’ (100) and ‘worst imaginable health state’ (0). EQ-5D is part of the UK Core outcome set^9^ and has been shown to be responsive to change,^10 11^ including when reported by proxy for those with cognitive impairment.^12 13^

#### Secondary outcome measures

HRQoL (EQ-5D-5L) at 1 and 12 months postinjury. Mortality, revision surgery and cause, and all complications will be obtained from the patients’ medical record. Patient interviews and questionnaires will be used to assess mobility status (walking ability indoors and outdoors) and residential status. An assessment of resource use will inform the economic analysis plan below.

### Sample size

The best available evidence we have from data collected during previously performed studies in this patient population suggests that the SD for EQ-5D-5L at 4 months postinjury is approximately 0.3 points.^10^ The best available evidence for what constitutes a minimal important difference (MID) for EQ-5D comes from a review of MID estimates.^14^ A review of the literature shows an estimated median value of 0.08 for the MID for EQ-5D. Using our previously established standard deviation (SD=0.33), this suggests a standardised effect size of approximately 0.24; a ‘small to moderate effect’ based on Cohen’s criteria.^15^ Assuming that the EQ-5D at 4 months postinjury has an approximate normal distribution, which Parsons *et al*
10 suggest is reasonable, and a 1:1 allocation ratio, then if the true difference between the experimental and control group EQ-5D means is in the range 0.07–0.08, we will need to recruit the below number of participants (see table 1) in each group to be able to reject the null hypothesis that the population means are equal with probability (power) 0.8 and 0.9 and type I error rate of 5% (significance).

**Table 1 T1:** Group sizes required following sample size calculations

Power, %	MCID		
	**0.07**	**0.075**	**0.08**
80	290	253	222
90	387	338	297

MCID, minimal clinically important difference.

Taking the intermediate minimal clinically important difference of 0.075, for 80% (90%) power, we would need to recruit 253 (338) patients in both the experimental arm and in the control arm, 506 (676) in total. In this population we expect considerable lost to follow-up due mainly to patients declining consent to further follow-up and incapacity, so we have assumed that only 60% of recruited study participants will be available at the definitive endpoint at 4 months. This gives a total sample size of 844 for 80% power and 1128 for 90% power. Conservatively, we aim to recruit 1128 to ensure 90% power based on these assumptions.

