**Methods and analysis:**

Multicentre (a minimum of seven UK hospitals), multisurgeon, parallel group, two-arm, superiority, randomised controlled trial. Patients aged 60 years and older with a displaced intracapsular hip fracture treated with hemiarthroplasty surgery are eligible. Participants will be randomly allocated on a 1:1 basis to either a cemented hemiarthroplasty or a modern hydroxyapatite coated uncemented hemiarthroplasty. Otherwise all care will be in accordance with the National Institute for Health and Care Excellence guidance. A minimum of 1128 patients will be recruited to obtain 90% power to detect a 0.075-point difference in the primary endpoint: health-related quality of life (EuroQol 5 dimensions 5 levels) at 4 months postinjury. The treatment effect will be estimated using a two-sided t-test adjusted for age, gender and cognitive impairment based on an intention-to-treat analysis. Secondary outcomes include mortality, complications including revision surgery and cause, mobility status, residential status, health-related quality of life at 1 and 12 months and health resource use. A within-trial economic analysis will be conducted.

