### Statistical analysis

The main analysis will investigate differences in the primary outcome measure, EQ-5D (HRQoL), between the two treatment groups on an intention-to-treat (ITT) basis at 4 months postinjury on a complete-case basis. The ‘death-adjusted’ ED-5D measure, imputing death as zero, is the preferred analysis option in this population, and will be used for all analyses.^16^ An initial analysis will test for differences between treatment groups using linear regression analysis, based on a Normal approximation for EQ-5D. Tests will be two sided and considered to provide evidence for a significant difference if p values are less than 0.05 (5% significance level). Estimates of treatment effects will be presented with 95% CIs.

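### Two unreconciled SDs for 4-month EQ-5D: Table 1 and the 1128 total use 0.30 (90% power for 0.075), the effect size uses 0.33 (about 84%)

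*Protocol article*

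**What the plan says.** All the inputs are in the Sample size section of the protocol article. Its opening sentence, citing earlier studies in this population, "suggests that the SD for EQ-5D-5L at 4 months postinjury is approximately 0.3 points". On the target difference it says: "A review of the literature shows an estimated median value of 0.08 for the MID for EQ-5D". The next sentence brings in a different SD: "Using our previously established standard deviation (SD=0.33), this suggests a standardised effect size of approximately 0.24".

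Table 1 then lists group sizes for differences of 0.07, 0.075 and 0.08, without naming the SD behind them: 290/253/222 at 80% power and 387/338/297 at 90%. The text settles on the middle column ("Taking the intermediate minimal clinically important difference of 0.075, for 80% (90%) power"), takes 338 per arm, assumes 60% of recruits are available at 4 months, and concludes: "Conservatively, we aim to recruit 1128 to ensure 90% power based on these assumptions".

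The Methods and analysis paragraph of the abstract repeats this without mentioning an SD: "A minimum of 1128 patients will be recruited to obtain 90% power to detect a 0.075-point difference in the primary endpoint".

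**The concern.** The standardised effect size and the group sizes describe the same comparison and should rest on the same SD. Here they do not, and nothing in the section tells the reader that the SD changed between the effect size sentence and the table.

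The combination of 1128 recruits, 90% power and a difference of 0.075 is the headline design claim. A reader who takes 0.33 as the planning SD, as the effect size sentence invites, will believe that the trial has 90% power at that SD. It does not. Planned power also colours how a non-significant result in a superiority trial is read, so the claim should be traceable to one stated input.

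**Working it through.** **Inputs.** SD 0.30 or 0.33; differences 0.07, 0.075 and 0.08; 1:1 allocation; 5% significance; 80% or 90% power; 60% availability at 4 months (all from Sample size). Two-sided testing is from Statistical analysis: "Tests will be two sided and considered to provide evidence for a significant difference if p values are less than 0.05".

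**Formula.** With the normal approximation, n per arm = 2 × (1.960 + z)² × SD² / difference², where z is 1.282 for 90% power. The two-sample t-test gives about one more per arm; its results are rounded up below.

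**Step 1: reproduce Table 1.**

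| SD | Power | 0.07 | 0.075 | 0.08 |
|---|---|---|---|---|
| 0.30, t-test | 80% | 289.3 → 290 | 252.1 → 253 | 221.7 → 222 |
| 0.30, t-test | 90% | 386.9 → 387 | 337.2 → 338 | 296.5 → 297 |
| 0.33, t-test | 80% | 349.8 → 350 | 304.9 → 305 | 268.1 → 269 |
| 0.33, t-test | 90% | 468.01 → 469 | 407.8 → 408 | 358.5 → 359 |

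SD 0.30 matches all six printed cells; SD 0.33 matches none. Solving the normal formula backwards from each printed cell gives an SD of 0.300 to 0.301.

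**Step 2: reproduce the totals.** 338/0.6 = 563.3, rounded up to 564 per arm, and 2 × 564 = 1128. Likewise 253/0.6 = 421.7, rounded up to 422, and 2 × 422 = 844. Both agree with the text.

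**Step 3: trace the effect size.** 0.08/0.33 = 0.242, the stated 0.24. With SD 0.30 it would be 0.08/0.30 = 0.267. So 0.33 was used in a calculation and is not simply a misprint. For the chosen difference of 0.075 the ratios are 0.075/0.30 = 0.25 and 0.075/0.33 = 0.227.

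**Step 4: power at 338 per arm under each SD.** The standard error is SD × √(2/338) = SD × 0.0769, and power is Φ(difference/SE − 1.960).

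- SD 0.30, difference 0.075: 0.075/0.02308 = 3.250; Φ(1.290) = 90.1% (t-test also 90.1%).
- SD 0.33, difference 0.075: 0.075/0.02538 = 2.955; Φ(0.995) = 84.0% (t-test 83.9%).
- SD 0.33, difference 0.08: 0.08/0.02538 = 3.152; Φ(1.192) = 88.3%.
- SD 0.33, difference detectable with 90% power: 3.242 × 0.02538 = 0.082.

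Intermediate SDs give intermediate power for 0.075 (t-test): 88.1% at 0.31 and 86.0% at 0.32.

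**The case against.** The strongest defence is that 0.30 is the better supported value. It carries a citation, is presented as the best evidence available, and is tied to this instrument at this time point. The 0.33 is described only as previously established, with no citation of its own, and the 0.24 derived from it feeds no later number. Everything the trial acts on (338, 676, 1128) is consistent with 0.30, so the faulty item may be the descriptive sentence and not the sample size. This stands. It is why the 84% can only be stated conditionally. It does not remove the inconsistency, because the section itself presents 0.33 as established and calculates with it.

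A reader might infer two stronger things. The first is that the trial is underpowered and really has 84% power. The document does not support that, since it gives no means of choosing 0.33 over 0.30. Reading the approximate 0.3 as a rounded 0.33 is possible, but nothing in the text confirms it. The second is that the section passes off a favourable SD as a cautious one, because it introduces the 1128 with *Conservatively*. In context that word follows the pair of totals, 844 and 1128, and describes taking the 90% option over the 80% option. It makes no claim about the SD and can stay.

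Two mitigations are also fair. Results are to be reported with 95% confidence intervals, which reflect the observed SD whatever was planned. The definitive analysis is also adjusted, which could lower the residual SD: going from 0.33 to 0.30 would need covariates explaining 1 − (0.30/0.33)² = 17% of the variance. That share is an assumption. The sample size section takes no credit for adjustment, and the analysis section allows baseline EQ-5D to be left out, so this possibility does not reconcile the two figures.

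**Conclusion.** The section is internally inconsistent as written: one SD supports the effect size, another supports Table 1 and the total. The arithmetic of the table and of the inflation for loss to follow-up is correct for SD 0.30. The stated 90% power for 0.075 therefore holds at 0.30 and falls to about 84% at 0.33, a type II error of about 16% in place of 10%. Even then, power is about 88% for the 0.08 taken from the literature, and the difference detectable with 90% power is only about 0.002 above it.

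These figures assume an unadjusted two-sided comparison of two means at 5% with exactly 338 evaluable per arm, the basis that reproduces Table 1. Which SD is right cannot be settled from the document. The finding is that the two must be reconciled; it is not that the trial lacks power.

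**What to change.** State one SD for 4-month EQ-5D, with its source, and make the effect size, Table 1, the text and the abstract agree with it.

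- **If 0.30 stands:** delete 0.33 and restate the standardised effect size as 0.25 for 0.075 (0.27 for 0.08). Table 1, the 1128 and the 90% power are unchanged.
- **If 0.33 stands:** correct Table 1 to 350/305/269 (80%) and 469/408/359 (90%), and say in the text and abstract that 1128 recruits at 60% availability give about 84% power for 0.075. Giving the companion figures (about 88% for 0.08, 90% for about 0.082) would help the reader. The totals quoted for 80% and 90% power at 0.075 would also need to follow the corrected table: 305/0.6 = 508.3, so 2 × 509 = 1018; and 408/0.6 = 680, so 2 × 680 = 1360. The sentence tying 1128 to 90% power would need rewording to match.

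The cost is a change of wording and at most one table, with a slightly lower stated power in the second case. No extra recruitment is needed, and no endpoint, allocation or analysis changes.

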### Statistical analysis

The main analysis will investigate differences in the primary outcome measure, EQ-5D (HRQoL), between the two treatment groups on an intention-to-treat (ITT) basis at 4 months postinjury on a complete-case basis. The ‘death-adjusted’ ED-5D measure, imputing death as zero, is the preferred analysis option in this population, and will be used for all analyses.^16^ An initial analysis will test for differences between treatment groups using linear regression analysis, based on a Normal approximation for EQ-5D. Tests will be two sided and considered to provide evidence for a significant difference if p values are less than 0.05 (5% significance level). Estimates of treatment effects will be presented with 95% CIs.

The stratification used for randomisation will ensure balance in treatment allocation across recruitment centres. In addition to the unadjusted analyses, we will also undertake regression analyses to adjust for any imbalance between treatment groups in patient baseline (preinjury) EQ-5D, age and gender. Age and gender are likely to be reported by all study participants, however, if baseline EQ-5D is poorly reported, such that it reduces the available sample size for the definitive analysis, then it will not be included in the definitive model. The fixed-effects analysis (linear regression model) will be generalised by adding a random effect for recruitment centre to allow for possible heterogeneity in patient outcomes due more generally to the recruitment centre. The adjusted mixed-effects regression will be the definitive (primary) analyses and will be reported as such. Analyses will be undertaken using the specialist mixed-effects modelling functions available in the software package R (http://www.r-project.org/).^17^ EQ-5D data will be assumed to be approximately normally distributed; possibly after appropriate variance-stabilising transformation. The primary focus will be the comparison of the two treatment groups of patients, and this will be reflected in the analysis which will be reported together with appropriate diagnostic plots that check the underlying model assumptions. Results will be presented as mean differences between the trial groups, with 95% CIs. The primary analysis will be on an ITT basis. However, a per-protocol analysis will also be undertaken by repeating the primary outcome analysis using the actual treatment received by participants (in contrast to the allocated treatment) as a sensitivity analysis to examine the robustness of conclusions to different assumptions about departures from the stated protocol.

In addition to the cross-sectional analysis at 4 months, we will also perform a longitudinal analysis of EQ-5D data collected at all study time points (1, 4 and 12 months) to a single value, namely the area under the curve (AUC) and facilitated comparisons of the AUCs between treatment groups. It is advisable in the presence of missing data to use summary statistics generated by mixed models, as estimates will not be biassed under the assumption that data are missing at random, or completely at random. Therefore, we will fit a repeated measures mixed model, with the same fixed effect structure as used in the primary analyses, but with a three level random effects structure where observations (time points) are nested within participants, and participants nested within recruitment centre.

It seems likely that some data may not be available due to voluntary withdrawal of patients, lack of completion of individual data items or general lost to follow-up. Where possible the reasons for data ‘missingness’ will be ascertained and reported. Although missing data are not expected to be a problem for this study, the nature and pattern of the missingness will be carefully considered—including in particular whether data can be treated as missing at random (MAR). If judged appropriate, missing data will be imputed using the multiple imputation facilities available in R.^18^ Any imputation methods used for scores and other derived variables will be carefully considered and justified. If the degree of missingness is relatively low, as expected, the primary analysis will be based on complete cases only (complete-case analysis), with analysis of imputed datasets used to assess the sensitivity of the analysis to the missing data. Reasons for ineligibility, non-compliance, withdrawal or other protocol violations will be stated and any patterns summarised. More formal analysis, for example, using logistic regression with ‘protocol violation’ as a response, may also be appropriate and aid interpretation.

Secondary analyses will be undertaken using the strategy described for the primary outcome for other approximately normally distributed outcome measures; for example, EQ-5D at 12 months. For dichotomous outcome variables, such as indicators of adverse events and other complications related to the trial interventions, mixed-effects logistic regression analysis will be undertaken with results presented as odds ratios (and 95% CIs) between the trial groups. The temporal patterns of any complications will be presented graphically and if appropriate a time-to-event analysis (Kaplan-Meier survival analysis) will be used to assess the overall risk and risk within individual classes of complications (eg, revision) and death. Cox’s proportional hazards regression will be used to test for differences in death rates between the trial intervention groups, after adjusting for age and gender. Multiple complications will be defined as two or more independent events, that is, not continuations of a previous complication, for the same patient and will be identified only after discussion with the clinical team.

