### Consent

Patients with a hip fracture are a clinical priority for urgent operative care. They undergo surgery on the next available trauma operating list. All patients with a fracture of the hip are in pain and will have received opiate analgesia. It is, therefore, understandable that the majority of patients find the initial period of their treatment in hospital confusing and disorientating. Similarly, patients’ next of kin, carers and friends are often anxious at this time and may have difficulty in absorbing the large amounts of information that they are given about the injury and plan for treatment. In this emergency situation, the focus is on obtaining consent for surgery (where possible) and on informing the patient and any next of kin about immediate clinical care. It is often not possible for the patient, relative or carer (consultee) to review trial documentation, consider the information and communicate an informed decision about whether they would wish to participate in the study. The consent procedure for this trial will reflect that of the surgery, with the clinical team assessing capacity before taking consent for the surgical procedure, and this capacity assessment then being used to guide the proper approach to consenting to the research. An appropriate method, in line with the mental capacity act and approved by the National Research Ethics Committee, will be used to gain either prospective or retrospective consent from the patient or appropriate consultee by a Good Clinical Practice (GCP) trained, appropriately delegated member of the research team.

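### The definitive model drops baseline EQ-5D if it is poorly reported, with no cut-off; keeping it with simple imputation is more precise and excludes nobody

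*Protocol article*

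**What the plan says.** All places are in the protocol article.

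- **Status of the model** (Statistical analysis): "The adjusted mixed-effects regression will be the definitive (primary) analyses and will be reported as such".
- **Covariates** (same section): the adjusted analyses "adjust for any imbalance between treatment groups in patient baseline (preinjury) EQ-5D, age and gender", with a random effect for recruitment centre.
- **Drop rule** (same section): "if baseline EQ-5D is poorly reported, such that it reduces the available sample size for the definitive analysis, then it will not be included". Age and gender are expected to be complete and carry no such condition.
- **Analysis set** (same section): the main comparison is "on an intention-to-treat (ITT) basis at 4 months postinjury on a complete-case basis", with deaths scored as zero.
- **Imputation** (same section): "If judged appropriate, missing data will be imputed using the multiple imputation facilities available in R". If missingness is low, as expected, the primary analysis uses complete cases, "with analysis of imputed datasets used to assess the sensitivity of the analysis to the missing data". Imputation is not linked to the baseline covariate.
- **Consent**: an approved method "will be used to gain either prospective or retrospective consent from the patient or appropriate consultee". The withdrawals section keeps data from participants who die before anyone has been approached about consent.
- **Abstract**: a different adjustment set without baseline EQ-5D, namely a "two-sided t-test adjusted for age, gender and cognitive impairment based on an intention-to-treat analysis".

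**The concern.** The rule is the only stated answer to missing baseline scores. It has no numerical cut-off, and it does not say who decides, when, or with what knowledge of allocation. The covariate set of the primary test therefore stays open until completeness has been inspected.

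The rule also treats the choice as one between losing participants and losing the covariate. Baseline EQ-5D is a preinjury measure. In a randomised comparison its missing values can be filled with a value that uses neither outcome nor allocation, and then neither is lost. Some missing baselines are plausible here, given emergency surgery, retrospective consent and early deaths that have a known outcome of zero. At stake is precision that the collected data could supply, together with a primary model fixed in advance.

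**Working it through.** **1. Reproduce the plan's figure.** The inputs from the Sample size section are a difference of 0.075, SD 0.30, two-sided 5%, 90% power and 60% available at 4 months. A two-sample t-test gives 338 per arm, and SD 0.30 reproduces all six cells of Table 1. Then 338/0.6 = 563.3, rounded up to 564, and 2 × 564 = 1128. No covariate gain enters this calculation.

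**2. Power if baseline is dropped.** The standardised difference is 0.075/(0.30 × √(2/338)) = 3.25. Power is Φ(3.25 − 1.96) = 90.1%. The planned power stands.

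**3. Simple formulas for the alternatives.** The correlation r between baseline and outcome and the missing share m are not in the article, so both are assumptions. Relative to a model with no covariates, and with values missing at random, the variance of the treatment effect is multiplied by:
- mean imputation, everyone kept: 1 − r²(1 − m)
- complete cases on baseline: (1 − r²)/(1 − m), which is below 1 only while m < r²

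Power at m = 20%, SD 0.30 and 338 per arm with an outcome:

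| r | Dropped | Complete cases on baseline | Mean imputation |
|---|---|---|---|
| 0.3 | 90.1% | 86.2% | 92.1% |
| 0.4 | 90.1% | 88.7% | 93.6% |
| 0.5 | 90.1% | 91.9% | 95.3% |

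Mean imputation was the best of the three at every r and m tried (r 0.3 to 0.7, m 5 to 40%).

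**4. Correct the comparator.** Step 3 flatters the gain, because the fallback still adjusts for age, gender and centre, and scoring deaths as zero can weaken the correlation. A simulation with age in both models, about 10% deaths scored zero, 15 to 20% of baselines missing and survivor correlations of 0.3 to 0.5 gave a variance reduction of about 5 to 14%. Taking 0.30 as the SD under the fallback:
- 5% reduction: 3.25/√0.95 = 3.334, power Φ(1.374) = 91.5%, equivalent to 1/0.95 = 1.05 times as many analysed participants
- 14% reduction: 3.25/√0.86 = 3.505, power Φ(1.545) = 93.9%, equivalent to 1/0.86 = 1.16 times as many

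The low end is sensitive to how far age already carries the information. With an age-baseline correlation of −0.35 and survivor correlations of 0.3 to 0.4, the reduction was about 3 to 7%.

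**5. Validity of the imputation.** In simulations with 338 per arm and about 20% of baselines missing, either at random or depending on the baseline value, mean imputation and the missing-indicator method estimated 0.075 to 0.076 for a true 0.075. Type I error was 4.8 to 5.5%.

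**6. Why complete cases on baseline is not the remedy.** Take early deaths of 7% versus 4%, all lacking a baseline score, 15% of other baselines missing, r = 0.4 and no effect in survivors. The unadjusted difference was 0.0167 and the mean-imputed one 0.0166, but the complete-case one was 0.0003. Excluding those deaths removes the mortality component that the death-adjusted outcome is meant to carry.

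**The case against.** The strongest defence is that the rule is written in advance and depends on completeness of a covariate, not on the treatment effect. Leaving a prognostic covariate out of a linear model in a randomised trial does not bias the estimate. The rule also protects the intention-to-treat set, because it avoids excluding people for a missing baseline. The sample size never counted on a gain from adjustment, unadjusted results will be reported as well, and multiple imputation is available. A cut-off could reasonably sit in an analysis plan that is not shown. All of this stands, and it keeps the point small. It does not show that dropping the covariate is the better method, and nothing in the article ties imputation to baseline EQ-5D.

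A reader might infer more than the text supports:
- **That any single missing value triggers the drop.** The condition is poor reporting that shrinks the sample, and a few missing scores need not count as poor reporting.
- **That loss of the covariate is almost certain.** The article gives no baseline completion rate. A preinjury rating can be recalled, and the Primary outcome measure section supports proxy report.
- **That the trial suffers both lost precision and excluded participants.** These belong to alternative branches of the rule and cannot both apply to one analysis.
- **That the gain is 6 to 22% of variance.** That is what 1 − r²(1 − m) gives for r 0.3 to 0.5 and m 10 to 30%, but against a model with no covariates, which is not the fallback.
- **That power starts at about 84%.** That uses the SD of 0.33 also quoted in the Sample size section. Which SD applies is a separate question, and Table 1 rests on 0.30.

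**Conclusion.** The point holds as a cheap improvement and not as the correction of an error. The rule leaves the primary covariate set open until completeness is seen and may discard a prognostic covariate without need. It introduces no bias and does not undercut the stated 90% power. The cost is some analyst freedom and a variance roughly 5 to 14% smaller forgone, which corresponds to power of about 91 to 94% in place of about 90% at SD 0.30. That size rests on assumed survivor correlations of 0.3 to 0.5, about 15 to 20% of baselines missing and about 10% deaths scored zero. With weaker correlation, or more overlap with age, it would be smaller. That baseline EQ-5D is prognostic is statistical judgement, since the article reports no correlation.

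**What to change.** Delete the drop rule. State that baseline EQ-5D is always in the definitive model, and that missing baselines are replaced by the overall or centre mean, pooled across arms and computed without outcome or allocation. Nobody with a 4-month outcome, including deaths scored zero, is then excluded for lack of a baseline score. Bring the abstract's covariate list into line in the same edit.

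The cost is one sentence of text and one line of code. The downside is small: mean imputation recovers only part of the gain that complete baselines would give, and it does nothing for participants whose 4-month outcome is missing.
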